#### Eligibility visit

2.3.5

For individuals with PTD/TS who are interested in the study, eligibility visits will be scheduled in person or via secure video with the study physician or neuropsychologist to confirm eligibility. If eligible, the Yale Global Tic Severity Scale (YGTSS) with tic inventory will also be completed (Storch et al., 2005).

#### Qualitative interviews

2.3.6

The qualitative interviews will be conducted individually with the study team and members of the Qualitative and Patient-Reported Outcomes (Q-PRO) Shared Resource. All interviews will be conducted via in-person or secure video. Interviews will be recorded to allow audio transcription for qualitative analysis. As mentioned previously, the exploratory questionnaire serves as the interview guide with questions adapted for age appropriateness and participant type. Topics covered include how tics make people feel, experiences at school, relationships with others, experiences at jobs, experiences with medical care, in public, or at home, and priorities for interventions.

Youth will be given time to answer sensitive questions confidentially. Youth will be asked about gender identity (for 12 and up), home environment, bullying, self-harm, risky behaviors, and their personal experiences. These answers will be confidential unless there is a concern that the there is a safety risk to themselves or others. At the end of the interview, participants will provide feedback regarding ease of completion, content, and completion time. Interviews are estimated to take 60–90 min to complete. Breaks will be provided as needed, and participants will be compensated for their time.

#### Qualitative analysis

2.3.7

Qualitative analysis will include transcribing verbatim and de-identifying all audio-recorded interviews in ATLAS.ti software. The study team will analyze the interviews using thematic content analysis practices (Green and Thorogood, 2018) to identify emerging themes and subthemes. Two study team members will develop a draft codebook including inductive and deductive codes, which will be reviewed and edited by the study team accordingly. Two study team members will then independently code the transcripts, meet regularly to discuss, and resolve discrepancies and reach a consensus. As needed, the PI (Principal Investigator) will serve as a third coder for unresolved discrepancies. Reports will be run for each code, and data will be reviewed within single codes or combination of codes to identify patterns and themes with the assistance of Q-PRO.

#### Feedback process

2.3.8

A total of 10 participants from Aim 1 will be invited to be the expert panel (two individuals with PTD/TS ages 8–17 years, two individuals with PTD/TS ages 18–30 years, two caregivers, two medical providers, and two advocates). A summary of the feedback process can be seen in Figure 2. We will use a holistic review to ensure diverse representation among the panelists. The main selection criteria will be the diversity of the panel member’s background or specialty, practice setting if applicable, geographic representation, minority representation, and absence of conflicts of interest. Panelists will complete the Delphi method through REDCap to maintain anonymity, minimize group conformity, and increase panelist comfort in providing their opinions.

**Figure 2 fig2:**
[figure not shown]
TD-STIGMA feedback process.

A concise list of indications and definitions will be provided to begin the Delphi method. A de-identified, alphabetized summary document of thematic content and narrative content analysis from Aim 1 will be securely emailed by blind-copying the panel to maintain anonymity and minimize bias. An initial indication matrix will be created from the exploratory questionnaire and proposed response options based on the Rand UCLA Appropriateness Method (Fitch, 2001). The panel will rate items on a Likert scale of 1–9 (1 = extremely inappropriate, 5 = uncertain, 9 = extremely appropriate). Each item will be rated separately for ages 8–17 and 18–30. The panel will also be asked to rate the proposed recall period and instructions.

During the first round of ratings, panelists will rate each item as described above and can provide open-ended survey responses on each question. Statistical analysis will synthesize the responses and content analysis of the open-ended responses will be conducted to identify any additional relevant information. The Rand UCLA criteria for agreement will be used. Disagreement is indicated by at least three panelists rating the indication in each extreme of the 9-point Likert scale.

During additional rounds, the panel will be provided with their responses, the frequency of the panel responses, and the panels’ anonymous comments. The individual rater will re-rate each item. We anticipate three rounds; however, additional closing criteria include achieving agreement and stability of responses for two rounds (Sekayi and Kennedy, 2017). The outcome of this process will be a close-ended TD-STIGMA scale. The Flesch Reading Ease (Flesch, 1948) score and Flesch–Kincaid Grade (Thomas et al., 1975) level will be used to assess questionnaire readability. We will aim for a fourth-grade reading level.

After the exploratory questionnaire item pool has been developed, the selection of items for quantitative analysis will follow an iterative process of expert and stakeholder reviews based on the Delphi Method. The comprehensive review of the items aims to establish face and content validities of the scale. We expect to eventually include 20 items for each version (young adult and youth) in the finalized questionnaire on *N* = 100 participants (*N* = 50 young adult and *N* = 50 youth).

#### Second interviews

2.3.9

The same recruitment methods will be used for the second interview. Participants with PTD/TS who participated in Interview 1 will be invited to participate again. Interviews will be scheduled in person or by secure video to complete the clinician administered YGTSS and inventory. The remainder of the study visit includes self-report and parent-proxy companion measures entered REDCap. The companion measures will be included to establish the psychometric properties of the TD-STIGMA scale. Participants will be compensated for their time.

##### Companion measures

2.3.9.1

The clinician-rated (YGTSS) is the gold-standard measure of tic severity. It is a clinician-administered, semi-structured inventory that measures tic severity and impairment over the past week. Motor and vocal tics are rated separately for their number, frequency, intensity, complexity, and interference on a 0–5 Likert scale. The total is summed to reflect motor tic severity (0–25), phonic tic severity (0–25), or combined tic severity (0–50). A single question rates tic-related impairment (0–50). The YGTSS displays excellent internal consistency, reliability, and convergent and divergent validity (Storch et al., 2005).

Quality of Life in Neurological Disorders (Neuro-QoL™) (Perez et al., 2007; Cella et al., 2011) instruments were developed through a collaborative, multi-site research initiative sponsored by the National Institute for Neurological Disorders and Stroke to construct psychometrically sound and clinically relevant health-related QoL measurement tools for individuals with neurological conditions. Through Neuro-QoL, the pediatric (Lai et al., 2012) and adult (Cella et al., 2012) stigma question bank is utilized. These are brief, reliable, valid, and standardized QOL assessments applicable across neurologic conditions. The adult bank has 24 questions for self-report, and pediatric (Lee et al., 2016, 2019; Ludlow et al., 2016, 2022; Lemelson and Tucker, 2017; Malli and Forrester-Jones, 2017, 2022; O'Hare et al., 2017; Lee and Park, 2019; Rodin et al., 2021) has 18 questions for self or parent report.

The Internalized Stigma of Mental Illness Inventory (ISMI) includes 29 items with five subscales assessing alienation, stereotype endorsement, discrimination experience, social withdrawal, and stigma resistance. Data analysis showed high internal consistency, test–retest reliability, and construct validity (Ritsher et al., 2003) as there are no validated discrimination measures in youth; adapted versions interchanging the word “mental illness” with persistent tic disorders are utilized for adult self-report and parent proxy reports. While changing the terminology and the age of use poses concerns for validity, in this study, we will gather proof of principle and preliminary data in preparation for future larger projects.

### Scale development method

2.4

Descriptive statistics will be used to examine TD-STIGMA item-level scores for detecting ceiling/floor effects, outliers, normality, and other problematic distributional characteristics. Such initial screening of the items may result in removing items that do not perform well (e.g., strong ceiling effect).

Following guidelines from the modified Consensus-based Standards for selecting health Measurement Instruments (Prinsen et al., 2018), we plan to evaluate the scale’s psychometric properties along several aspects of validity. The assessment of face and content validities is described in the section Feedback Process. Confirmatory factor analysis (CFA) will also assess the structural validity for the hypothesized domains-- structural, community, interpersonal, and individual levels of stigma and discrimination (Figure 1). We do acknowledge the smaller sample size. However, given the relatively rare disease and that the domains in CFA have been identified in prior literature we felt it was appropriate. A fifth protective domain will include protective measures against stigma and discrimination. Missing values for the CFA will be treated as missing-at-random, and the full information maximum likelihood method, in which only those variables observed for a case would enter the estimation procedure, will be used to maximize efficiency. We will use multiple commonly accepted goodness-of-fit indexes to evaluate if the *a priori*-determined factor structure is valid (Hu and Bentler, 1999). We also plan to conduct a bifactor analysis (Gibbons and Hedeker, 1992). Because most of the items in TD-STIGMA will be adapted from validated instruments, we expect only minor adjustments (e.g., item removal) will be needed to establish the structural validity for the domains in TD-STIGMA. The subscale score will be formed from the sum score of the items under the subscale, and the unweighted sum of subscales will form the overall score.

We expect missing values to be minimal. If the proportion of missing items exceeds 50%, the participant will not receive a score and will be excluded from all analyses. Internal consistency will be evaluated using Cronbach’s alpha at the item and the subscale/scale level. The intraclass correlation will assess test–retest reliability by retesting a subset of clinically stable participants (*n* = 20) 2 weeks after test administration. We expect the test–retest intraclass correlation coefficient to be above 0.70 (Paiva et al., 2014). Items may be removed if that criterion is not achieved. Both convergent validity and known-group validity will be evaluated. Convergent validity will be evaluated by assessing the correlation coefficients between the subscale/scale of TD-STIGMA and the companion measures. We plan to use the criterion based on the ISMI for assessing criterion validity. We will use a cutoff of 2.5 on the ISMI scale (Ritsher et al., 2003; Boyd et al., 2014; Bengochea-Seco et al., 2018), of which the total score range is 0 to 4, 4 being the worst, to indicate the presence of stigma. We will compare the means of TD-STIGMA of the stigma and the non-stigma groups using a t-test. We hypothesize that TD-STIGMA is higher in the stigma group identified by ISMI. The analyses will use the SAS 9.3 statistical software and Mplus v8.

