#### Development of exploratory questionnaire

2.3.4

An initial set of 44–47 stigma questionnaire items was developed using domains of interest, clinical expertise, and gaps in the literature and modeled from validated stigma scales. The Questionnaire on Anticipated Discrimination (QUAD) (Gabbidon et al., 2013), Discrimination and Stigma Scale (DISC) (Bakolis et al., 2019), PaedS (Kaushik et al., 2017), PMHSS (McKeague et al., 2015), and specific questions of the Internalized Stigma of Mental Illness (ISMI) (Ritsher et al., 2003) were used as models for stigma questions. Items were created to include perceived and experienced stigmatization of the individual with PTD/TS at each level of the SEM: individual, interpersonal, community, and structural. Examples of selected questions are provided in Table 1.

**Table 1 tab1:** Selected examples from exploratory questionnaire TD-STIGMA questions – youth and young adults.

**SEM level**	**Question**	**Perceived stigmatization?**	**Experienced stigmatization?**
Structural	How are you treated at a doctor’s office, hospital, or medical facility because of your tics?	X	X
Structural	What are the biggest misunderstandings people have about your tics?	X	
Structural	Do you feel your doctors understand your tics?	X	
Community	How does having tics impact your experiences in public?	X	X
Community	What barriers have you encountered to getting the treatments recommended by your doctor for your tic disorder?	X	X
Community	Have you been treated differently by your school because of your tics?	X	X
Community	What impact does your tic disorder have on your ability to work?	X	X
Interpersonal	How does having tics impact relationships?	X	X
Interpersonal	What does having Tourette Syndrome or tics mean to your family?	X	
Individual	What does having a tic disorder mean to you?	X	
Individual	How does having tic disorder make you feel as a person?	X	

The exploratory questionnaire covers several domains, including experienced and perceived stigmatization at each SEM level, positive psychosocial factors (*In what ways do having tics make you stronger? What has been most helpful for you in coping with your tics?*), contributing or confounding stigmatization risk factors (*gender identity, sexual identity for adults, sociodemographic* var*iables*), and intervention priorities (*What do you feel would be most helpful in addressing some of the challenges you have mentioned?*)

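### Scores are plain sums given to anyone with up to half the items missing, with no proration stated, so taken literally a partly answered form can score half of what its answers imply

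*Protocol article*

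**What the plan says.** All the scoring rules are in section 2.4, Scale development method, of the protocol article.

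- Subscale: "The subscale score will be formed from the sum score of the items under the subscale".
- Total: "the unweighted sum of subscales will form the overall score".
- Missing items: "If the proportion of missing items exceeds 50%, the participant will not receive a score and will be excluded from all analyses". Scores are withheld only above 50%, so a respondent at exactly 50% is scored.
- Factor analysis: "Missing values for the CFA will be treated as missing-at-random", using full information maximum likelihood (FIML), in which "only those variables observed for a case would enter the estimation procedure". This is stated for the factor analysis and for nothing else.
- Amount of missing data: "We expect missing values to be minimal". No figure is given.

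Section 2.3.8, Feedback process, gives the planned length: "We expect to eventually include 20 items for each version (young adult and youth) in the finalized questionnaire".

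Section 2.4 names four stigma domains and a fifth, protective domain. It does not say in which direction the protective domain enters the total. It also does not say whether the 50% is counted over the whole scale or within each subscale. Response options are still to be rated by the Delphi panel, so item coding is open.

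**The concern.** A tolerance of 50% missing items goes naturally with a mean or a prorated score. Paired with a sum, it lets the number of items answered drive the score. Two respondents with the same average answer get different totals if one of them skipped items.

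The scores feed nearly all of the validation: correlations with the companion measures, the t-test between groups defined by the ISMI cutoff, and the retest intraclass correlation in 20 stable participants. In the retest, answering a different number of items on the two occasions looks like change. Section 2.4 expects that coefficient to exceed 0.70 and allows items to be removed if it does not, so a scoring artefact could cost the scale sound items. Later users of the scale would also inherit the scoring rule.

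There is a second, smaller point. Participants above 50% missing are removed from every analysis, including the factor analysis, where FIML could use the items they did answer. The article itself acknowledges that its sample of 100 is small.

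**Working it through.** The plan gives no figure on this point to reproduce, so the check is on the scoring arithmetic, followed by illustrative simulations.

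**1. Who is scored.** Expected items: 20 (section 2.3.8). Threshold: more than 50% missing means no score (section 2.4). 0.50 × 20 = 10, so a respondent with 10 blanks is scored. One with 11 (11/20 = 55%) is not.

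**2. Effect on one respondent.** Let *m* be the number of missing items and *a* the mean of the answered items.

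- Literal sum = (20 − *m*) × *a*
- Prorated sum = 20 × *a*
- Ratio = (20 − *m*)/20, independent of *a* and of the coding

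| Items missing | Literal sum as share of prorated |
|---|---|
| 1 | 95% |
| 2 | 90% |
| 4 | 80% |
| 5 | 75% |
| 10 | 50% |

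Example with assumed coding 0–4 and a mid-scale answer of 2: 10 × 2 = 20 against 20 × 2 = 40. With coding 1–5 and an answer of 3: 10 × 3 = 30 against 60. With coding from 0, a blank counts like the lowest answer. With coding from 1, it counts below the lowest possible answer.

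**3. Level of the threshold.** Assume 20/5 = 4 items per domain. If the 50% is counted over the whole scale, 10 blanks could empty two subscales (8 items) in a scored participant. If it is counted per subscale, 2 of 4 may be blank. The share can fall to half under either reading; only the wholly empty subscale needs the whole-scale reading.

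**4. Effect on the total (simulation).** Assumptions: n = 100, 20 items coded 0–4, loading 0.65, latent correlation with the criterion 0.6, affected respondents missing 1 to 10 items at random, 800 replicates.

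| Respondents affected | Correlation: complete / literal sum / prorated | Standardised group difference: complete / literal sum / prorated |
|---|---|---|
| 5% | 0.573 / 0.558 / 0.572 | 1.068 / 1.037 / 1.067 |
| 10% | 0.573 / 0.547 / 0.572 | 1.070 / 1.011 / 1.068 |
| 20% | 0.574 / 0.527 / 0.572 | 1.073 / 0.969 / 1.069 |

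At 20% affected, the mean score falls from 40.0 to 37.8. Proration recovers almost all of the loss.

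**5. Effect on a short subscale (simulation).** Assumptions: 4 items coded 0–4, loading √0.35, latent criterion correlation 0.65, whole-scale threshold, an empty subscale summed as 0. For the retest, the blank occurs on one occasion only and half of the item-specific variance is stable.

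| Respondents with the subscale blank | Correlation | Retest intraclass correlation |
|---|---|---|
| none | 0.52 | 0.81 |
| 5% | 0.47 | 0.72 |
| 10% | 0.42 | 0.64 |
| 20% | 0.35 | 0.50 |

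Of 20 retested participants, 10% is two people, enough in this example to move the coefficient below 0.70. These values depend on the assumed response distribution and are orders of size, not forecasts.

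**The case against.** The strongest reply is that the article nowhere says a missing item counts as zero. It says what a score is built from and who receives one. A half-items rule is compatible with a prorated sum, and a condensed article may leave that step to a full protocol, analysis plan or scoring manual. This stands in part: the zero contribution is an inference from a literal sum. But the article did fix both a sum and a numerical cut-off, and applied together as printed they give the result above.

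A reader might go further and infer several things that the article does not support:

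- *Blanks will be read as absence of stigma.* That needs zero-fill and stigma items coded from 0. Neither is stated.
- *The 50% applies to the whole questionnaire.* The level is not given.
- *Missingness will be structural because some respondents do not work.* The question "What impact does your tic disorder have on your ability to work" comes from Table 1 of section 2.3.4, the open-ended questionnaire that serves as the interview guide. The closed scale is a later product of the Delphi rounds, with items rated separately by age group and response options still open. Inapplicable items are possible, not shown.
- *The error always lowers the score.* If protective items reduce the total, skipping them raises it.

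On size, the article expects few missing values. The standard error of a correlation near 0.6 with n = 100 is about (1 − 0.6²)/√99 = 0.064. The loss of 0.573 − 0.558 = 0.015 at 5% affected is about a quarter of that, so the effect on the total would be hard to see. Even so, it is a systematic loss that a larger sample does not remove, and the argument is weaker for short subscales.

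Finally, dropping mostly blank forms is a legitimate choice of analysis set. Removing them from the factor analysis is inefficient rather than contradictory.

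**Conclusion.** The point holds in a limited form. Followed as written, the sum rule and the 50% tolerance can give a respondent as little as half the prorated score, and nothing stated outside the factor analysis corrects this. That ratio rests only on the expected 20 items and on a literal sum.

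The effect on results depends on missingness that the article does not quantify. If missingness is minimal, the effect on the total is small (about 0.57 to 0.56 in the 5% scenario). For subscales of about four items it can be material, including for the 0.70 retest criterion, but only if whole subscales are left blank and still scored. The direction for protective items depends on how that domain enters the total. Severity: minor to moderate.

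**What to change.** In section 2.4 (or the analysis plan, if it governs scoring):

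1. Score each subscale as the mean of its answered items, multiplied by its number of items if a sum metric is wanted, and only when at least 50% of that subscale's items are answered.
2. Form the total only when all its subscales are scorable, and state the direction in which the protective domain enters it.
3. Limit the exclusion above 50% missing to score-based analyses, and let the FIML factor analysis use the items those participants answered.
4. If any final item can be not applicable, for instance on work or school, give it a response code separate from the lowest answer.

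The cost is a few sentences and possibly one extra response code in REDCap, which must be in place before the scale is administered. The downside is that a few participants may lose a total score. Proration also assumes that unanswered items would have resembled the answered ones in the same subscale, which is why the threshold belongs at subscale level.

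### Items may be removed when the retest ICC in 20 people misses 0.70, and with no other retest sample the recomputed ICC would be biased upward

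*Protocol article*

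**What the plan says.** All the relevant text is in the protocol article.

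- **The retest (section 2.4, Scale development method).** Test–retest reliability is assessed by an intraclass correlation, "retesting a subset of clinically stable participants (*n* = 20) 2 weeks after test administration". No other retest data are described.
- **The criterion (same section).** "We expect the test–retest intraclass correlation coefficient to be above 0.70". No confidence bound is attached, so it reads as a point estimate.
- **The consequence of missing it (same section).** "Items may be removed if that criterion is not achieved". The article gives no rule for which or how many items may go and no confirmation step. It does not say which ICC, before or after removal, is the reported result.
- **The score (same section).** "The subscale score will be formed from the sum score of the items under the subscale", and the overall score is the unweighted sum of the subscales. Dropping an item therefore changes the score whose ICC is judged.
- **The number of items (section 2.3.8, Feedback process).** "We expect to eventually include 20 items for each version (young adult and youth) in the finalized questionnaire".

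**The concern.** The same 20 people would decide whether items are removed, supply the evidence on which items to remove, and be the only source of a revised ICC. Choosing items on retest data and then estimating reliability from those data favours items whose two scores happened to agree in this sample. The revised ICC is then too high on average, even if no item is worse than another.

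Two things are at stake. First, reliability is a main purpose of the study: the introduction (section 1.2) makes later intervention work depend on being able to measure stigma reliably, so an optimistic ICC would carry forward. Second, section 2.3.8 uses the Delphi rounds to establish face and content validity. Removal prompted by a noisy threshold could take out items that the panel chose to keep.

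**Working it through.** The article gives no precision or power calculation for the retest, so there is no stated figure to reproduce.

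**Inputs from the article:** n = 20, two occasions, threshold 0.70, about 20 items per version, sum score.

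**Assumptions not in the article:** the true ICC, the split of item variance, how items are chosen, and the maximum number removed.

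**Step 1. Precision at n = 20.** For a one-way ICC with k = 2, F = (1 + ICC)/(1 − ICC), with 19 and 20 degrees of freedom.
- Observed ICC 0.70: F = 1.70/0.30 = 5.667.
- The 97.5% points are F(19, 20) = 2.482 and F(20, 19) = 2.509.
- Lower: 5.667/2.482 = 2.283, and (2.283 − 1)/(2.283 + 1) = 0.39.
- Upper: 5.667 × 2.509 = 14.217, and (14.217 − 1)/(14.217 + 1) = 0.87.

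The 95% CI is 0.39 to 0.87. The same formula gives 0.23 to 0.82 for an observed 0.60 and 0.57 to 0.92 for 0.80.

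**Step 2. Chance of exceeding 0.70 with no removal.** P = Pr[F(19, 20) > 5.667/((1 + ρ)/(1 − ρ))] for true ICC ρ. At ρ = 0.60 this is Pr[F > 5.667/4 = 1.417] = 22%.

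| True ICC | P(observed > 0.70), n = 20 |
|---|---|
| 0.50 | 8% |
| 0.60 | 22% |
| 0.65 | 34% |
| 0.70 | 50% |

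**Step 3. Chance of exceeding 0.70 with removal in the same 20 people.** This was simulated with 20 exchangeable items, so that any gain from removal is chance. If the total-score ICC is 0.70 or less, the item whose deletion raises it most is dropped. This repeats until the ICC exceeds 0.70 or the cap is reached. Two variance structures were used:
- *Model A* (ICC(2,1), 800 runs per setting): trait 0.30, stable item-specific 0.25, occasion state 0.196, error 0.254. True ICC 0.600.
- *Model B* (one-way ICC): trait 0.22, stable item-specific 0.15, state 0.13, error 0.50. True ICC 0.595.

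| Items removable | Model A | Model B |
|---|---|---|
| 0 | 22% (exact, step 2) | about 20–22% |
| up to 3 | 33% | about 39% |
| up to 5 | 44% | about 49–51% |

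In Model A the unpruned rate was 19.5% and 24.2% in two separate runs. The Monte Carlo standard error at 800 runs is √(0.22 × 0.78/800) = 1.5 points, so both are compatible with 22%. Among Model A samples that first missed 0.70, 17% (cap 3) and 26% (cap 5) were lifted above it by chance, with mean apparent gains of 0.055 and 0.083. The true ICC after five deletions was 0.598.

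**Step 4. Sensitivity at true ICC 0.60, cap 5.** Five-category items: 23% to 48%. Model A with trait share 0.15: 26% to 64%. The shift was upward in every setting.

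**Step 5. Items that are not equally stable.** Suppose 3 of 20 items are dominated by transient state (trait 0.05, state 0.45; other items 0.30 and 0.12). Up to 3 greedy deletions then raise the mean *true* ICC from 0.592 to 0.651. With 5 such items and up to 5 deletions it rises from 0.549 to 0.650. In samples brought above 0.70, however, the true ICC was only about 0.63–0.64.

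**The case against.** The strongest case on the other side has four parts.

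- **The wording is permissive.** The text says items may be removed. It describes no repeated search, and it does not say that the ICC will be recomputed and declared met. A reader might infer that items are dropped until the ICC passes, but the article does not say so. A condensed article may also leave the deletion rule and the reported ICC to the full protocol. This stands, and it limits the claim to what the rule permits. It does not remove the point, because the article itself ties removal to a threshold in one sample of 20.
- **Removing unstable items is normal scale development.** A reader might infer that pruning cannot improve true reliability. That holds only if items are equally stable, and step 5 shows real improvement when they are not. This stands, and it is why removal should not be barred. The optimism of the recomputed ICC remains.
- **The size rests on the assumed cap.** Under Model B, caps of 1 and 2 items give only about 28% and 32%. Section 2.4 expects only minor adjustments such as item removal, although it says this about structural validity. Large caps have no basis in the text and are not used here.
- **The purpose is partly preliminary.** Section 2.3.9.1 speaks of proof of principle, but about the adapted ISMI. The small-sample acknowledgement in section 2.4 concerns the factor analysis. Neither addresses the retest.

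**Conclusion.** The point holds in a limited form. The article permits item removal prompted by missing a point-estimate criterion in 20 people, and it describes no other people in whom the shortened scale could be retested. An ICC recomputed after such removal is biased upward. With a true ICC near 0.60, equally stable items and greedy deletion, the chance of an observed value above 0.70 goes from about 20–22% to about 33–39% (up to 3 items) or 44–51% (up to 5). The direction was the same in every setting tried. The size depends on the variance structure, the selection method and the cap, none of which the article states.

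Two further readings are tempting but unsupported. One is that only about 10 people per questionnaire version are retested: the article gives 20 with no split. The other is that the earlier screening, "Such initial screening of the items may result in removing items that do not perform well", belongs to the same problem: it concerns distributional faults such as ceiling effects, not the retest, and is ordinary practice.

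This should be changed, because it can bias a reported property of the scale and the remedy is cheap.

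**What to change.** Keep the option to remove items, and add to section 2.4:

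1. The test–retest result is the ICC with its 95% CI, computed on the item set fixed after distributional screening and confirmatory factor analysis and before any retest-based removal. It is reported whether or not it exceeds 0.70.
2. If items are then removed using retest data, the post-removal ICC is reported beside that result. It is labelled exploratory, or corrected for optimism by a bootstrap that repeats the removal step.
3. The post-removal ICC is not used to declare the 0.70 criterion met.

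The change is to wording and reporting, with no extra participants or visits. The bootstrap, if chosen, adds some programming. The downside is that the reported ICC may be less favourable.
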